## Safety Monitoring

We have not had any serious adverse events in the two clinical trials we have conducted, nor have any been reported in additional publications using this model[38-40](#_ENREF_38) since the original report was published[35](#_ENREF_35). Vital sign monitoring, inpatient observation, and outpatient follow-up (calls at 1 day and at 7+2 days after discharge) will be performed as we have published previously. The study will be terminated for any volunteer who experiences a SAE as defined above.

An independent, internal DSMB will monitor this trial. The DSMB will include senior investigators with expertise in critical care and infectious diseases. The DSMB will make recommendations to ensure data integrity and the safety of the volunteers.

DSMB Activities:

1) Review the research protocol and approve plans for data and safety monitoring.

2) Evaluate the progress of the study, including periodic assessments of data quality and timeliness, participant recruitment, accrual and retention, participant risk versus benefit, and other factors that can affect study outcome. Monitoring will also consider factors external to the study when interpreting the data, such as scientific or therapeutic developments that may have an impact on the safety of the participants or the ethics of the study. The principal investigator will make available to the DSMB any newly published information related to the use of endotoxin, pioglitazone, or zileuton which may affect patient safety.

3) Make recommendations to Washington University School of Medicine, the IRB, and investigators concerning continuation or conclusion of the trial.

4) Submit an annual report to the IRB.

5) Protect the confidentiality of the trial data and the results of monitoring.

6) Review data and safety issues (including any and all adverse events) and determine, with information provided by the study staff, whether the events should be regarded as study-related or unrelated. The DSMB will be empowered to stop the study, at their discretion, for safety reasons.

DSMB meeting frequency: The DSMB will meet to review the above listed information after the first two patients. They will then decide whether the study can go forward as planned, whether modifications are to be made in any procedures, and when to review the next set of data (but not less than every 8 patients).

Stopping rules: The study will be stopped *for any individual subject* in the case of any SAE, defined prospectively. New recruitment/enrollment will be discontinued after any SAE until satisfactorily reviewed by the DSMB. The DSMB will make recommendations, if any, for changes to recruitment practices, the informed consent document, or safety/monitoring practices. All such recommendations will be communicated to the IRB, RDRC, and CRU.

The FDA will be notified of any study stoppages. Recruitment for study participation will resume *only* when we have received clearance from the FDA to do so. The entire study will be discontinued completely in the event of any study-related life-threatening event or death.

- 1. **Collecting/reporting of adverse events**

In the study in normal volunteers, all adverse experiences, whether expected or unexpected, will be recorded in the case report form (see Appendix III for samples) and reported to the DSMB for this study. Any adverse experience that occurs to a greater severity than expected will be reported to the IRB, RDRC, CRU, and FDA.

The IRB (Washington University School of Medicine Human Research Protection Office), RDRC, and CRU will be notified of any SAE within 10 working days of occurrence. The FDA will be sent an IND Safety Report within 10 working days of occurrence of any SAE. If the event is fatal or life threatening, the DSMB, IRB, and RDRC will be notified of the event within twenty-four hours. The CRU and FDA will be notified by telephone no later than 3 days after occurrence.

The IRB, RDRC, CRU, and FDA will receive annual reports regarding all adverse experiences.

- 1. **Follow-up of serious adverse events**

All SAEs will be followed up until resolution or permanent outcome of the event. All follow-up information will be included in the case report form.

## Potential Risks

### 5.6.1. Risks associated with bronchoscopy and bronchoalveolar lavage

General:

Potential risks are related to both the administration of the medications necessary to perform the procedures (discussed later), plus those related to the actual procedure of bronchoscopy itself. The risks associated with the procedure are:

*Likely:* Coughing (at times severe) is the most common side effect of bronchoscopy. Hoarseness, loss of voice and sore throat are often experienced temporarily after bronchoscopy.

*Rare:*These include allergic reactions to drugs administered, low blood oxygen, increased heart rate, palpitations, irregular heart rhythm, pneumonia, fever, rigors, abnormalities in chest X-rays, difficulty breathing, respiratory failure, airway spasm and narrowing, trauma to the nose, airway, or lung, or death.

### 5.6.2. Risks associated with bronchoalveolar lavage

*Likely:* BAL usually causes a slight decrease in oxygen levels in the blood for up to a couple of hours after BAL. This may affect breathing and exercise capacity.

*Less Likely:*Post-BAL fever, sudden onset of stiffness, and a vague feeling of bodily discomfort has been reported in 10%-30% of patients 4-6 hours after the procedure. This usually resolves within 24 hours.

### 5.6.3. Risks associated with medications/drugs

**Endotoxin (intrabronchial instillation, 4 ng/kg):**

*Likely:*Mild to moderate respiratory symptoms which may include cough, difficulty breathing, chest pain, wheezing, or excessive secretions. These are expected to last less than 48 hours. Other side effects are also expected to last less than 24 hours. These include: mild fever, mild decrease in heart rate and blood pressure, a slight decreased ability to absorb oxygen into the body, and mild or moderate head-ache, muscle aches, and a vague feeling of bodily discomfort.

*Rare:* Endotoxin in the blood stream at high levels can cause serious reactions such as shock and death. Endotoxin in the lungs at high levels can cause reactions similar to severe pneumonia, leading to low oxygen levels, need for breathing machine support, heart attacks, brain damage, and death. However, there have been no deaths reported when endotoxin has been used in the manner described here for research purposes. There have also been no deaths reported when endotoxin has been administered intravenously or to the lungs in a mist during approved research protocols. [name]. is the Sponsor-Investigator for the IND (#100042) from the FDA for the bronchoscopic instillation of endotoxin (E. coli O:113, NIH Clinical Center Reference Endotoxin [CCRE]) into a lung segment of healthy volunteers. An amendment will be filed to add the protocols required for this proposal to the IND.

**Antibiotics used to decrease bacteria in the lung**(each normal volunteer will only receive one type, 1 dose 12 hours prior to and a second dose immediately prior to bronchoscopy):

Oral sulfamethoxazole*/*trimethoprim (80/400):

*Less Likely:*Allergic skin reactions to this medication are common and include rash, itching and sensitivity to the sunlight. Many people experience nausea, vomiting, or loss of appetite. Some people have developed liver problems when taking this medication.

*Rare:*Some people have experienced mental and nervous system side effects, which have included confusion, depression, hallucinations, seizures, difficulty with coordination, and fever. There have been reports of blood abnormalities related to taking this medication. Rarely, people have developed a severe allergic reaction (Steven-Johnson Syndrome) which included a severe rash, sores in their mouth, diarrhea, and inflammation of their digestive tract. This is more likely with longer use of the drug. Kidney inflammation resulting from taking this drug has been reported.

*This is a “sulfa” drug. As such, people with allergies to sulfa containing drugs may experience severe allergic reactions to it. In addition, people with G6PD deficiency can develop severe anemia from taking this drug. The side effects listed above are much less likely when the drug is taken only for one day, as in this protocol.

Oral amoxicillin:

*Less Likely:*Rash can occur in people who are allergic to this drug or who have an active infection with mononucleosis. Some people have developed diarrhea from taking this medication. Occasionally this drug has decreased a person’s ability to fight certain types of bacteria, resulting in a severe infection. There have been reports of mental and nervous system side effects, which have included seizures and fevers.

*These side effects are much less likely when the drug is taken only for one day, as in this protocol.

**Medications used prior to bronchoscopy** (each subject may receive one or more of these):

These medications are used according to standard policy and procedures for the performance of bronchoscopy at Barnes-Jewish Hospital. Research participants may receive Meperidine HCl (Demerol), Hydroxyzine (Vistaril), and Inhaled Lidocaine, 1% and 2%:

*Likely:* Common side effects include: dry nose, mouth, or throat, low blood pressure, lightheadedness, dizziness, drowsiness, constipation, nausea, vomiting, or weakness.

*Less Likely:*Occasionally people experience difficulty swallowing, sore throat,headache, stomach cramps, hunger, diarrhea, abdominal pain, nervousness, confusion, fatigue, difficulty urinating, difficulty breathing, pain at injection site, joint aches,or tremor.

*Rare***:** Rare reactions that have been reported include racing heartbeat, irregular heartbeat, eye pain, blurred vision, sensitivity to light, water retention, rash, angioedema (swelling around eyes and throat), numbness, cough, bloody nose, shock, mental depression, excitement, sedation, coma, agitation, hallucinations, or seizures.

**Medications used during bronchoscopy for sedation** (each participant may receive one or more of these): Midazolam HCl (Versed) and Fentanyl:

*Likely:*Common side effects include pain at injection site, hiccups, low blood pressure, slow heartbeat, drowsiness, nausea, vomiting, constipation, or slower breathing.

*Less Likely:* There is a slight chance that participants may experience headache, cough, blurred vision, dizziness, lightheadedness, abdominal cramps, difficulty breathing, excitement, confusion, loss of memory, irregular heartbeat, or their heart could stop beating.

*Rare:* Rare reactions that have been reported include convulsions, rash, wheezing, cold and clammy skin, difficulty urinating, rapid heartbeat, or mental confusion.

**Test drugs.** The following drugs are commercially available and FDA-approved. They are designated “test” drugs in the context of this research study.

Pioglitazone:

Adverse reactions reported for pioglitazone are based on chronic administration (at least 16 weeks, typically 26 weeks or longer) in patients with diabetes. It is expected that these reactions will be less likely with the 14-day total treatment protocol required for this study.

*Less Likely:* Upper respiratory tract infection, headache, sinusitis, myalgia, pharyngitis.

*Rare:* Hypoglycemia, heart failure, edema, pain in extremity, back or chest (these were seen with chronic administration of the drug in patients with diabetes; these are expected to be highly unlikely in healthy volunteers receiving this drug for 2 weeks). An increased risk of bladder cancer has been observed in patients taking this drug for at least 12 months or longer.

Zileuton:

Adverse reactions reported with zileuton are based on chronic administration (12-week treatment or longer). It is expected that these reactions will be less likely with the 5-day total treatment protocol required for this study. Small studies with treatment periods similar to the one used in this protocol have not reported adverse effects related to zileuton treatment.

*Less Likely:* Sinusitis, nausea, nasopharyngeal pain, gastrointestinal disorders (upper abdominal pain, diarrhea, dyspepsia, vomiting), rash, hypersensitivity, hepatotoxicity, headache, upper respiratory tract infection, low white blood cell counts.

*Rare:* Severe hepatic injury resulting in death, life-threatening liver injury with recovery, symptomatic jaundice, hyperbilirubinemia, and elevations of ALT over 8x upper limits of normal (case reports).

### 5.6.4. Risks associated with PET/CT imaging with [18F]FDG

Scan itself:

*Less likely:*Some people may find lying flat or wearing the pneumatic bellows device to be uncomfortable and experience shoulder or back discomfort as a result. The participant will need to lie flat for ~1½ hours for the PET/CT scan. If the pneumatic bellows device is the reason for discomfort, it will be removed. If the subject cannot tolerate lying flat at all, the study will be discontinued.

Exposure to radiation:

*Likely:*The amount of radiation exposure each person will receive from a 10 mCi injection of [18F]FDG plus the attenuation-correction CT scan and a second end-inspiration CT scan over the lungs for a single PET/CT session is equivalent to a uniform whole-body exposure of 0.55 rems. With the second low-dose CT scan, the total dose for 2 PET/CT plus 2 CT scans to complete the PET/CT imaging protocol for this study (total 2.0 rems), this is equivalent to ~40% of the allowable annual dose for radiation workers.

*The risk from radiation exposure of this size is too small to be measured directly. Participants will be provided with a “Radiation Fact Sheet” supplied by the Washington University School of Medicine, Division of Nuclear Medicine.

Radioactive Drugs:

[18F]FDG is an FDA-approved drug that is given in such small (“trace”) amounts that they have no known harmful effect. PET/CT scans with this tracer are performed routinely for clinical indications with no associated adverse effects reported in the history of its use.

It was recently reported by the FDA that the CT scans may cause the malfunction of electronic medical devices. However, volunteers with such implanted devices will be excluded from participating in this study.

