**Exploratory Endpoints**

- CT density (in Hounsfeld Units, HU)
- Airway thickness
- Respiratory-gated standard uptake value (SUV)
- Presence of TLR4 polymorphisms

1. **SUBJECTS**
   1. **Inclusion Criteria**

- Healthy man or woman, any race or ethnicity, age 19 – 44 years old
- Screening FEV1 and FVC >= 90% of predicted
- Screening oxygen saturation by pulse oximetry >97% on room air
- Capable of lying still and supine within the PET/CT scanner for ~1.5 hours
- Capable of following instructions for breathing protocol during CT portion of PET/CT
- Able and willing to give informed consent
- BMI < 35
  1. **Exclusion Criteria**
- Pregnancy (confirmed by qualitative urine hCG pregnancy test)
- Lactation
- History of cardiopulmonary disease
- Currently taking any prescription medications
- History of tobacco use or illicit drug use within the past year
- Presence of implanted electronic medical device
- Enrollment in another research study of an investigational drug
- Known allergy to pioglitazone or zileuton
- Known allergy to both trimethoprim/sulfamethoxazole and amoxicillin
- Known allergy to drugs routinely used during bronchoscopy
- History of chronic active liver disease or acute liver disease within the past 3 months
- SGOT >47 IU/L, SGPT > 53 IU/L, or bilirubin > 1.1 mg/dl
- Inability to lie flat for 1.5 hours for PET/CT scans or follow breathing protocol instructions for the CT portion of the PET/CT
- Prior research-related radiation exposure within the past year such that participation in this study would result in exposures that exceed the limits as defined by the FDA RDRC regulations (21 CFR 361.1)
  1. **Women of Child-Bearing Potential**

We will confirm pregnancy test results in all women of child-bearing potential screened for this study. Women who meet the following criteria may also be enrolled without a screening pregnancy test:

- Post-menopausal status defined as women who are 40 years of age or older and have been amenorrheic for at least 2 years
- Women who have had a hysterectomy and/or bilateral oophorectomy
- Women who have been surgically sterilized with no unintended pregnancies for at least 2 years after the procedure
  1. **Number of Subjects**

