**Day 3:**

1. The subject will have blood drawn in the morning for repeat testing of CBC, CMP, CRP and ESR. Additional blood will again be drawn for research lab assays. Any values outside normal expected values (see exclusion criteria) will be reviewed by one of the investigators, and a decision will be made concerning whether continued observation in the hospital is required or out-patient follow-up is needed until resolution. A urine sample will again be obtained for the same research lab assays as above.
2. If the second i.v. placed on Day 1 is not still functioning, a second i.v. catheter will be placed in the subject’s arm for the PET study.
3. The last dose of pioglitazone/placebo and zileuton/placebo will be administered in the morning.
4. A small drop of blood will be taken to check a blood glucose level.
5. FDG-PET/CT and second CT scan will be obtained in exactly the same manner as was done on Day 1 of this study.
6. Pulmonary function tests will be obtained.
7. The volunteer will be escorted back to his/her room at the CRU and will begin preparation for the 2nd bronchoscopy, which is for the bronchoalveolar lavage.
8. The subject may receive “pre-op” medications (Demerol, Vistaril) before the bronchoscopy as well as medication during the bronchoscopy (Versed and fentanyl). This will be at the discretion of the study physician to reduce any discomfort during the bronchoscopy.
9. During the bronchoscopy, the subject’s vital signs and oxygen saturation will be monitored closely. Oxygen will be administered to maintain their saturation level per protocol.
10. After the bronchoscopy and bronchoalveolar lavage (BAL), the subject will be monitored closely for the next several hours. Intravenous fluids will be maintained until the patient can tolerate oral medications and nutrition. After 4 hours of monitoring, if he/she is clinically stable, the monitors will be removed and s/he will be allowed to eat. Once fully recovered from the medications, the study physician will determine if the volunteer meets the criteria to be discharged to go home or whether s/he should remain in the CRU for overnight observation.

During the study, the volunteer will have PFTs measured after endotoxin instillation but prior to the BAL. BAL will not be performed if the FEV1 has decreased >20% from the pre-endotoxin baseline value. The change in pulmonary function will be followed until resolved or stabilized.

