### 5.6.5. Risks associated with blood draws, intravenous catheter insertion, non-invasive tests

Chest radiograph

*Likely:* The volunteer will be exposed to a small amount of radiation (0.01 rem), which is 0.2% of the allowable annual dose for radiation workers.

*The risk from radiation exposure of this size is too small to be measured directly. Participants will be provided with a “Radiation Fact Sheet” supplied by the Washington University School of Medicine, Division of Nuclear Medicine.

Blood draws and i.v. catheter insertion:

*Less Likely:* The insertion of a needle into a vein sometimes causes discomfort, bruising, or bleeding at the site of needle insertion. Occasionally some people experience dizziness or feel faint when a needle is placed in their arm.

*Rare:*The insertion of a needle into a vein rarely causes inflammation or infection.

Spirometry:

*Less Likely*: The effort required for a good spirometry test may cause shortness of breath. However, participants will be allowed to take rest breaks between measures if needed. Occasionally, during spirometry, people have experienced dizziness, wheezing, chest pain, racing or pounding heart, an upset stomach, severe shortness of breath, or coughing.

*Rare:*Rarely, people have fainted during spirometry. The test will not be continued in such a case.

Pregnancy:

The medications used for the bronchoscopy and the radiation exposure can cause birth defects and mental retardation to a fetus. All women volunteers for this study will have had a negative pregnancy test prior to further participation.

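### The radiation dose per scanning session (0.55 rem) and the study total (2.0 rem) in Protocol 5.6.4 do not reconcile

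*Protocol*

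**What the plan says.** Protocol section 5.6.4 states the dose for one imaging session. The sentence counts the exposure "from a 10 mCi injection of [18F]FDG plus the attenuation-correction CT scan" and then continues: "a second end-inspiration CT scan over the lungs for a single PET/CT session is equivalent to a uniform whole-body exposure of 0.55 rems". On its wording, 0.55 rem covers three components: tracer, attenuation-correction CT and end-inspiration CT.

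The next sentence opens by referring to the second low-dose CT and gives "the total dose for 2 PET/CT plus 2 CT scans to complete the PET/CT imaging protocol for this study (total 2.0 rems". It adds that "this is equivalent to ~40% of the allowable annual dose for radiation workers".

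The imaging section (PET-CT Imaging with [18F]FDG) places one end-inspiration CT at the end of each acquisition. The timeline has one such session on Day 1, and for Day 3 it says: "FDG-PET/CT and second CT scan will be obtained in exactly the same manner as was done on Day 1 of this study". The table of procedures shows FDG-PET scans on Days 1 and 3 only.

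Two other places bear on the point. Section 5.6.5 describes the chest radiograph as a "small amount of radiation (0.01 rem), which is 0.2% of the allowable annual dose for radiation workers". Section 3.2 (Exclusion Criteria) excludes anyone whose prior-year research exposure is such that "participation in this study would result in exposures that exceed the limits as defined by the FDA RDRC regulations".

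**The concern.** Both sentences in 5.6.4 describe the same two tracer injections and the same four CT scans, yet doubling the first figure does not give the second. The people exposed are healthy volunteers, and the section exists to state their exposure. Someone who works from the per-session figure gets a total 45% below the one the protocol states (0.90 / 2.0).

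The criterion in 3.2 also combines past research exposure with what this study adds. It can be applied in only one way if there is one study dose, and 5.6.4 supports two.

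**Working it through.** **Inputs**
- Dose per session, d = 0.55 rem (5.6.4), described as including both CTs.
- Number of sessions, n = 2 (timeline, Days 1 and 3; table of procedures).
- Stated total, T = 2.0 rem, about 40% of the annual worker limit (5.6.4).
- Chest radiograph: 0.01 rem, 0.2% of the same limit (5.6.5).

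**Step 1. Reproduce the percentage.** The limit implied by the radiograph is 0.01 / 0.002 = 5 rem. The limit implied by the total is 2.0 / 0.40 = 5 rem. The two agree, so 2.0 rem, about 40% and a 5 rem base are consistent with one another.

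**Step 2. Rebuild the total from the sessions.** n × d = 2 × 0.55 = 1.10 rem. As a share of the limit, 1.10 / 5 = 22%. The stated total is not reproduced.

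**Step 3. Size of the gap.** 2.0 − 1.10 = 0.90 rem, and 2.0 / 1.10 = 1.82. Read the other way, 2.0 / 2 = 1.0 rem per session against the stated 0.55.

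**Step 4. Could rounding explain it?** If 0.55 stands for 0.545 to 0.555, two sessions give 1.09 to 1.11 rem. If 2.0 stands for 1.95 to 2.05, the ranges do not come close to meeting.

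**Step 5. Other combinations**

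| Reading | Total (rem) |
|---|---|
| Two sessions plus the chest radiograph: 1.10 + 0.01 | 1.11 |
| Three doses of 0.55 | 1.65 |
| Four doses of 0.55 | 2.20 |
| 0.55 leaves out the end-inspiration CT, each such CT adding x: 1.10 + 2x = 2.0 | 2.0 if x = 0.45 |

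Only the last row reaches 2.0 rem. It requires the per-session sentence to be wrong in naming the end-inspiration CT, and it uses a CT dose of 0.45 rem that the protocol nowhere gives.

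**Step 6. Consequence for the exclusion criterion.** Let L be the applicable limit, which the protocol does not state as a number. The prior exposure that still allows entry is L − 1.10 under one figure and L − 2.0 under the other. The two disagree for prior exposure between L − 2.0 and L − 1.10, a band 0.90 rem wide wherever L lies (given L of at least 2.0). Assuming L = 5 rem, borrowed from the implied worker limit, the band runs from 5 − 2.0 = 3.0 to 5 − 1.10 = 3.9 rem. The chest radiograph would shift both ends by only 0.01 rem.

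**The case against.** The strongest reply is that the total is sound and one clause is misplaced. The second sentence introduces the low-dose CT as if it were an addition and lists two PET/CTs plus two CTs. If 0.55 rem covers only the tracer and the attenuation CT, and each end-inspiration CT adds 0.45 rem, everything closes at 2.0 rem and 40%. This is plausible and may well be what happened, but it cannot be confirmed because no separate CT dose is given. Even if it is right, the per-session sentence as printed is wrong and needs correcting.

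A second reply is that 2.0 rem is the only study total stated, so staff applying the exclusion would naturally use it. If 2.0 were too high, the error would be conservative: exposure over-disclosed and entry made tighter. That is fair, and it limits the practical harm. It does not help if the total is the correct figure and someone relies on the lower per-session one.

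A reader might infer three stronger things:
- **That the true total is 1.10 rem.** The protocol's other figures point the other way.
- **That participants or the radiation committee were given conflicting doses.** The consent form, the fact sheet and the committee submission are not available to this review, so this cannot be shown.
- **That ineligible volunteers would be enrolled.** This depends on a numerical limit the protocol does not give and on prior exposures that may be rare.

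**Conclusion.** The inconsistency is real and the text does not resolve it: 1.10 rem by summing the sessions against 2.0 rem as stated, a difference of 0.90 rem, or 22% against 40% of the implied 5 rem limit. The agreement of 2.0 rem with the two percentages makes the per-session figure, or the list of what it includes, the likelier error. This is an indication only. The 40% may simply have been calculated from 2.0 rem, so the agreement does not verify the dosimetry.

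The effect on eligibility is conditional. It reaches only volunteers with substantial research exposure in the past year, about 3.0 to 3.9 rem if the limit is assumed to be 5 rem. The protocol uses 5 rem implicitly for radiation workers and does not state it as the RDRC limit. How many candidates fall in that band is unknown and may be few.

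Endpoints, sample size and efficacy analyses are untouched. The point is worth correcting because it is a safety figure for healthy volunteers and an eligibility rule draws on it.

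**What to change.** Check both figures against the dosimetry already on file, by component (tracer, attenuation-correction CT at 30 effective mAs, end-inspiration CT at 50 effective mAs) and by session. A fresh calculation is needed only if that record does not settle the matter. Then reconcile the two sentences in 5.6.4 so that the per-session dose names exactly what it includes and two sessions add up to the total, and restate the percentage from the verified total.

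Use that one total when applying the prior-radiation exclusion in 3.2, and confirm that any participant and committee documents carry the same number. Which figure is correct is for the dosimetry to decide.

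The cost is a dosimetry check and a wording amendment. Nothing in the design or analysis changes.
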